#### RQ2. Risk factors for PD

**a) DNA analysis**TraPCAf recruitment will link with the Global Parkinson’s Genetic Program (GP2) (www.gp2.org) and the Aligning Science Across Parkinson’s (ASAP) initiative (www.parkinsonsroadmap.org). The ASAP initiative is devoted to accelerating the pace of discovery and informing the path to a cure for PD through collaboration, research-enabling resources, and data sharing. GP2 is a resource programme of the ASAP initiative focused on improving understanding of the genetic architecture of PD and making this knowledge globally relevant.In summary, genome-wide association studies and related genomics explorations will be conducted utilising DNA extracted from whole blood and/or saliva samples. The aim of this collaboration is to contribute 1000 samples across TraPCAf sites (plus 2000 samples from healthy controls), which will be shared with GP2 for analysis and sequencing, contributing to GP2’s goal to genotype more than 150,000 unique samples from diverse populations.We will work closely with our CEI team to determine how best to return genetics results for variants whose significance is known (i.e., clinically relevant information) to PwP and understand what follow up and counselling is available in-country. Where expertise is lacking, we will work with GP2 to build capacity in genetic counselling. Anonymised genotypic data will be linked with phenotypic data and microbiome analyses. The primary outcome will be the Odds ratio (or Hazards ratio) of specified single nucleotide polymorphisms (SNPs) measured as the frequency of polymorphic variation in PwP versus controls (based on the genotyping results from the NeuroChip® [53] genotyping platform). Genome-wide analysis data comparing PD and controls will also be reported as an outcome by the TraPCAf research team in collaboration with GP2.**b) Microbiome and metabolite analysis**Stool samples and buccal swab samples will be collected using standardised equipment across all sites from all consenting participants for 16S sequencing for microbiome analysis and metabolite analysis [54]. All datasets obtained will be identified to bacterial species-level operational taxonomic units (OTUs) to differentiate the faecal community composition of individuals from the rural and urban communities under study. Analysis pipeline to capture microbiota data on alpha diversity, beta diversity, differential abundance of microbial taxa and functional gene will be utilised [54]. Primary outcome (conducted at baseline) will be the difference between cases and controls. In conjunction with microbiome and metabolite analysis, a questionnaire on diet and medication use (see supplementary information) developed for the purposes of addressing TraPCAf research questions will be administered. Samples will be linked to individuals’ genotypic and phenotypic data to allow for further analysis.**c) Pesticide, heavy metal and trichloroethylene analysis**To estimate the impact of environmental exposures on the development of PD, water and soil samples will be collected using standardised procedures from the homes of identified participants who consent. This will primarily involve participants recruited through the prevalence study but those attending outpatient clinics will also be invited to participate in this study aspect and given the equipment and instructions to collect and bring samples from their homes to their next clinic visit. Samples will be analysed for pesticide content, heavy metal content and the presence of trichloroethylene. In conjunction with the analysis, the mini-environmental risk factor questionnaire (MERQ-PD) [55] will be administered in a case–control design and analysed alongside pesticide data from collected samples. A pesticide and heavy metal exposure questionnaire, developed by the TraPCAf team for the purposes of addressing the research question (supplementary material), will also be administered to understand historical toxin exposure.Urine samples will also be collected from consenting participants at the clinic visit and analysed for pesticide residue levels to determine individual exposure. Levels will be compared to previously published results indicating potentially dangerous exposure. Inclusion of urine samples will provide an indication of body burden but also of recent and continued exposure levels. Environmental risk factors for PD will be measured at baseline using (i) toxicology assessment for contaminants of emerging concern related to PD (including pesticides, herbicides, other chemicals) in the soil and water samples at residences of PwP versus healthy controls and (ii) comparison of the risk exposures of PwP and controls based on responses in the MERQ-PD questionnaires and reported as the relative risk of exposure for each subcategory of risk factors interrogated.

#### RQ3. Aids to diagnosis for PD

We will explore the diagnostic utility (predictive values) of several innovative methods for improving the clinical diagnosis of PD. These include the use of biological markers, as well as technological methods (see Table 2). Primary outcome measures for the sub-studies exploring aids to diagnosis will include the diagnostic utility, positive predictive value, accuracy of diagnosis of PD versus normal control, area under Receiver Operating Characteristics (ROC) curve, negative predictive values, sensitivity, and specificity of the diagnostic modalities described. For all study aspects within this RQ, consenting participants will be invited to provide samples, or to trial the technology tools.**a) Biological diagnostic tools****Plasma, serum, saliva, and urine analysis** Aggregated alpha-synuclein in brain and peripheral nervous system tissue is a diagnostic feature of PD. We are collaborating with a team at Newcastle University, through registered partner company ‘ESP Diagnostics’ (www.espdiagnostics.com) who have developed an assay for extra-cellular synucleinopathic protein (ESP), that detects recombinant alpha-synuclein aggregation using a fluorescent dye (covered by patent rights (WO2019/171035A10)). This works on urine, blood plasma and blood serum samples, requiring equipment available in most hospital biochemistry laboratories (for further information on the sensitivity and specificity using saliva see [56, 57]). Blood will be taken using standard blood-taking equipment by a research nurse. For saliva, the participant will spit into a tube. Urine will be collected in a plastic beaker. All samples will then be prepared, aliquoted and stored appropriately.**Metabolome analysis** Metabolomics is the analysis of small molecule metabolites contained within cell, tissue and biofluid systems. PwP may have a particular odour, and this is currently being investigated at the University of Manchester (www.mbc.manchester.ac.uk/barrangroup). We are collaborating with the team leading this work to investigate whether metabolites can be used to diagnose PD [22, 58] (covered by patent rights US20230077659A1 and US20230080918A1). The team have developed a diagnostic platform, using mass spectrometry, that can classify PD from sebum samples with up to 78–88% accuracy (for detailed methodology see [22, 59]). Briefly, sebum samples will be taken by a research nurse with a cotton bud rubbed on the upper back (a sebum-rich area of the body) for metabolite analysis. Primary outcomes for this analysis (conducted at baseline) will be the diagnostic utility of skin metabolites measured in sebum in differentiating PwP from controls. Metabolome samples will also be linked with phenotypic and genotypic data. It is important to determine whether the “PD signature” identified is a pure disease-related signature and will be detected in Africans with PD, despite genetic, epidemiological, and dietary differences. Findings will confirm the more widespread utility of swabs as a methodology to help diagnose PD and provide a unique window into underlying pathophysiology. This could be particularly useful in Africa, as samples remain stable at room temperature for several weeks, facilitating storage and transport.**b) Technology diagnostic tools****Digital mobility outcomes** Gait assessment can discriminate and predict early disease, track disease progression, and identify therapeutic response in PD [60]. Wearable technology (such as accelerometers and inertial measurements units (IMUs)) offer a low-cost, unobtrusive solution to record the signals needed to extract comprehensive gait features in laboratory and real-world scenarios. Widespread development and adoption of commercial sensors by the public for activity monitoring demonstrates their feasibility and acceptability in HICs, but these technologies have been under-utilised in LMICs to date. Axivity AX6, a low-cost non-invasive wearable device (www.axivity.com/product/ax6) which is a data logger capable of recording raw data from a suite of integrated sensors) [61, 62] will be used to objectively monitor mobility (walking activity and gait) during free-living mobility in PwP. This study aspect will initially be rolled out to participants in Ghana, and potentially other sites based on initial outcomes. Briefly, the sensor is secured to the participant’s lower back (see [61] for image of placement) who will be advised to continue with their usual activities and not change their routine, with monitoring over 7 days [63]. The device quantifies digital mobility based on walking speed, step count, walking bout number and duration, for example. The device has previously been validated in the UK [62, 64] and piloted in people with frailty in Tanzania [61], demonstrating feasibility. Based on previous estimates (pilot in Tanzania), we will initially recruit 50 PwP from the Ghana sites. Gait assessments will also be used to monitor disease progression as part of RQ4.**NeuroMotor Pen (NMP)** The NMP is a hand-held medical device, developed by ‘Manus Neurodynamica’ (www.manusneuro.com), with a unique patented system combining sensor technologies in a digital pen with software and an analytical engine with Decision Support System. The interface enables users to non-invasively record parameters of minute limb and hand motion from graphical tasks and apply automated analysis, with high reproducibility [65]. These parameters are used as ‘digital biomarkers’ to provide objective information about movement abnormalities. The NMP, designed with a specific intended use in the clinic, assesses and quantifies motor skills based on simple copying (writing and drawing) tasks that are not dependent on literacy. Unlike wearables, the NMP measures subtle symptoms that cannot easily be seen or quantified with the naked eye and provides a test of the extrapyramidal system. Symptoms currently recorded with the UPDRS, such as bradykinesia and tremor, can be objectively quantified with NMP. Previous research suggests that the NMP is a quick, inexpensive, non-invasive and objective aid to diagnosis [66]. The NMP has undergone two phases of clinical validation in European cohorts with high differential diagnostic sensitivity (PD vs not PD) (80%) and high specificity (75%). This technology will be initially piloted with participants in 2 sites, and rolled out to additional sites after the feasibility of use in lower resource settings is better understood.**Optical coherence tomography (OCT) imaging** People with confirmed and prodromal PD have been reported to have changes in retinal structure [67]. Retinal imaging via OCT is a quick, non-contact, inexpensive method to detect these changes. It is an infra-red based imaging technology with no eye drops required, making it well tolerated. Yet, retinal changes have yet to be used to detect neurological disease or monitor progression [68]. In this work, we propose to build on advanced statistical models developed by our collaborators in the ‘OCTAHEDRON’ project at Newcastle University (www.research.ncl.ac.uk/octahedron) to automatically identify biomarkers of PD diagnosis in retinal OCT scans [69]. Such tools have been developed using data mainly from the eyes of individuals in white populations from high-income countries. We aim to validate and tune these models to ensure they also serve the health needs of LMIC populations [70]. The increased accessibility of OCT imaging in lower resource settings highlights the relevance for diagnostic and disease monitoring. In addition, data collected will allow the exploration of biomarkers for present and future disease progression to maximise the impact of limited clinical resources. All sites with this equipment available, and with the necessary expertise to carry out retinal imaging, will be able to enrol participants to this study aspect.**Oxford smartphone application** The ‘Oxford Parkinson’s Disease Centre’ in the UK (www.dpag.ox.ac.uk/opdc) have piloted, tested and refined a 6-min smartphone test of motor symptoms in 522 participants with early PD, prodromal Rapid Eye Movement (REM) sleep behaviour disorder (RBD) and age-matched controls, showing accuracies of 85–92% in distinguishing PD versus control and RBD versus PD [71]. Using novel machine learning algorithm MLA data approaches, they can use this smartphone test to predict motor Unified Parkinson’s Disease Rating Scale (UPDRS) with a high level of accuracy, and to predict clinically relevant change, such as the onset of falls, 18 months before occurrence, with positive predictive values around 90% [72]. The applicability of this smartphone application to the African context will be initially tested in 4 sites, and rolled out to additional sites once usability is better understood. The app could be used to accurately distinguish PD from controls (and PD from idiopathic REM sleep behaviour disorder), providing a growing consensus for the utility of digital biomarkers in early and prodromal PD, which could be of particular use in settings where specialised clinicians are lacking. The smartphone application will also be used to monitor progression as part of RQ4

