There have been few PD prevalence studies (most from several decades ago) and no community-based incidence studies in sub-Saharan Africa (SSA) [13–15]. Methodological flaws including the small population sizes surveyed and preponderant reliance on hospital-based data have given the erroneous impression that PD is rare in Africa. The recently published World Health Organization (WHO) technical brief, +‘Parkinson disease: a public health approach’, [16] alludes to the inconsistent data available on PD from low- and middle-income countries (LMICs), and the consequent difficulty of estimating the true burden in Africa or providing convincing data to motivate governmental policy makers and donor agencies to prioritise PD on the continent. Better understanding of the prevalence of PD in communities would justify prioritising PD, inform national policies, improve awareness of the disease, improve diagnostic rates, and access to health services, and drive the focus on providing access to pharmacological and non-pharmacological treatments (e.g., physiotherapy). Until now, there has only been one large scale prevalence study of PD in SSA, based on a house-to-house survey in Hai, Tanzania, in which less than a quarter of people with PD (PwP) had previously been diagnosed [17]. Furthermore, identifying the challenges and needs of PwP and their families in different countries and contexts [7, 8] would drive the narrative for local evidence-based policies [3].

Africa faces a stark gap in the provision of appropriate neurological workforces and trained physicians [18], care, rehabilitation and treatment, making life for PwP very difficult [19]. Awareness about PD is generally very low among the population [8, 20, 21] and healthcare professionals, resulting in under- and delayed diagnosis [10]. Exploring efficient and effective methods for diagnosing PD [22] (including use of telemedicine [23, 24] and/or novel biomarkers) could facilitate diagnosis at the primary care level, while offering opportunities for early management [16]. Sustainable medication is largely inaccessible and unaffordable across the continent [18, 25–28], however, investigations into alternative sources of levodopa (e.g., *Mucuna Pruriens* (MP)) have yielded positive results [29, 30].

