#### Processes for recruitment

PwP identified through outpatient clinics, and through prevalence studies, will be invited to participate in TraPCAf, will be provided with information sheets on each of the different aspects of the research (see Table 2), and be able to consent to particular study aspects. The clinical assessment (part of RQ4) is the minimum involvement a participant can have. Consenting participants can, but do not need to, participate in all study aspects. Furthermore, 2 healthy population controls of the same ethnicity, matched for gender and age will be recruited for every 1 PwP, providing the same biological and environmental samples as PwP (RQ2 and RQ3), and undergoing the same clinical assessments (RQ4).

The inclusion criteria for the prevalence studies are:1. Consenting resident in the delineated community for at least 12 months prior to the date of survey.2. Age 18 years or older for Tanzania, Kenya, Ghana (no upper limit) and > 40 for urban Lagos site.

Inclusion criteria for PwP in all studies are:1. Consenting adults aged 18 years or older (no upper limit) diagnosed with PD based on UK Parkinson’s Disease Brain Bank (UKPDBB) clinical diagnostic criteria [51] of any stage.2. For the *Mucuna Pruriens* trial, PwP should be treatment naïve (summary of inclusion criteria detailed in RQ6 section below).

Inclusion criteria for healthy controls are:1. Consenting healthy, neurologically normal (assessed at in-person physical examination) adults aged 18 years or older (no upper limit) who are age, gender and ethnicity matched (per country).

Prospective participants will be excluded if they do not consent or lack capacity to consent (clinical judgment), and/or are physically unable to complete study procedures due to advanced disease and physical disability. Participants will provide details of medical comorbidities, if known, during the clinical examination.

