
#### RQ4. Clinical phenotype and progression of PD

**a) Clinical assessment**All PwP, either previously or newly diagnosed from each site, will be invited to a detailed examination and assessment using standard disease specific questionnaires, e.g., the International Parkinson and Movement Disorders Society Unified PD Rating Scale (MDS-UPDRS) (see Table 3), in addition to study-specific questionnaires developed by the research team (see supplementary material). At yearly intervals we will follow up these cohorts, including monitoring for disease progression (MDS UPDRS and Hoehn and Yahr scale) and cognitive decline (using Intervention for Dementia in Elderly Africans (IDEA) and Montreal Cognitive Assessment (MoCA) scores), assessing response to treatment, reviewing compliance with medication, and assessing motor symptoms (MDS-UPDRS total and Part III scores) and non-motor symptoms (MDS-NMS) [73].

**Table 3 Tab3:** Data collection tools to be administered during clinical examination and assessment

Tools and questionnaires
Clinical observations^a^
Neurology assessment^a^
Questionnaire on women’s symptoms^a,b^
Healthcare resource use questionnaire^a,c^
MDS Unified PD Rating Scale (**MDS-UPDRS**) [74]
Clinical impression of severity index (**CISI-PD**) [75]
MDS Non-Motor Symptoms Scale (**NMSS**) [76]
Barthel index [77]
Intervention for Dementia in Elderly Africans (**IDEA**) cognitive screening tool [78]
Mini-environmental risk factor questionnaire (**MERQ-PD**) [55]
Questionnaire on pesticide exposure^a^
Questionnaire on microbiome^a^
PD Questionnaire (**PDQ-8**) [79]
EuroQol- 5 Dimension instrument (**EQ5D-5L**) [80]
REM sleep behaviour disorder questionnaire (**RBDSQ**) [81]
Hospital Anxiety and Depression Scale (**HADS**) [82]
Montreal Cognitive Assessment (**MoCA**) [83]
PD Sleep Scale (**PDSS**) [84]
Epworth Sleepiness Scale (**ESS**) [85]
Questionnaire for impulsive-compulsive disorders in PD – Rating Scale (**QUIP-RS**) [86]
Scales for outcomes in PD – Autonomic (**SCOPA-AUT**) [87]

^a^Unvalidated questionnaires developed (based on expertise) for the purposes of addressing TraPCAf research questions (see supplementary material)

^b^Questionnaire developed and adapted from the Fox insight ‘Experience of women with PD’ survey [88]

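### The primary sebum and microbiome contrasts pool treated and untreated PwP against healthy controls, so on their own they cannot show a purely disease-related signature; an untreated-PwP comparison should be prespecified

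*Protocol article*

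**What the plan says.** **Cases.** Under Processes for recruitment, PwP are adults "diagnosed with PD based on UK Parkinson’s Disease Brain Bank (UKPDBB) clinical diagnostic criteria [51] of any stage". Only for the *Mucuna Pruriens* trial does that section add that "PwP should be treatment naïve". RQ4 confirms the mix: "All PwP, either previously or newly diagnosed from each site, will be invited to a detailed examination and assessment". Recruitment runs through neurology outpatient clinics in all seven countries and through community surveys in four.

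**Controls.** Two per case, healthy and without neurological abnormality on examination, matched on age, gender and ethnicity. They give the same samples and undergo the same assessments.

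**Primary outcomes.** For stool and buccal samples (RQ2 b): "Primary outcome (conducted at baseline) will be the difference between cases and controls". For sebum (RQ3 a, Metabolome analysis), the primary outcome, also at baseline, "will be the diagnostic utility of skin metabolites measured in sebum in differentiating PwP from controls". Neither is restricted, stratified or adjusted by PD medication or stage in the text shown.

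**Aim.** The sebum text asks whether the PD signature "identified is a pure disease-related signature and will be detected in Africans with PD, despite genetic, epidemiological, and dietary differences". It names genetic, epidemiological and dietary differences, but not treatment.

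**Supporting data.** RQ2 b includes a questionnaire on diet and medication. RQ4 records MDS-UPDRS and Hoehn and Yahr. Both sample types are linked to phenotype. RQ1 invites survey-diagnosed PwP to the other sub-studies. Data analysis and management foresees multivariable modelling in general terms.

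**The concern.** A neurologically normal control has no reason to take levodopa or another PD drug. That is an inference, since the article does not state it, but a safe one. Any effect of PD drugs on skin metabolites or gut flora therefore appears only on the case side and becomes part of the case-control difference. The stated primary outcome and the stated question do not match.

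This matters for use as well as for biology. RQ3 wants aids that raise diagnosis rates, and people still to be diagnosed are by and large not yet on PD drugs. The Background notes that in the earlier Hai survey "less than a quarter of people with PD (PwP) had previously been diagnosed". A classifier whose accuracy comes partly from drug traces would look good in a pooled sample that includes treated clinic patients and do worse in the people it is meant for. A taxon that differs because of medication could likewise be reported under RQ2 as a PD risk factor.

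**Working it through.** The article gives no figure to reproduce on this point: no treated share, and no sample size or accuracy target for either comparison. The check is structural, followed by illustrations on assumed inputs.

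**1. What the groups identify.** Classify people by disease and by PD drug use.
- Controls: no disease, no drug.
- Untreated PwP: disease, no drug.
- Treated PwP: disease and drug.
- Nobody is in the fourth cell (drug without disease).

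Let d be the mean difference between untreated PwP and controls, h the mean difference between treated and untreated PwP, and t the treated share of sampled cases. Then:
- pooled case-control difference = d + t × h
- untreated PwP minus controls = d
- treated minus untreated PwP = h (mixed with stage unless stage is made similar)

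The pooled contrast returns one number for two unknowns. If d = 0 it still shows t × h. Controls say nothing about h, so a drug term in a model must be estimated within PwP. Such a model works only through the untreated PwP, and that comparison is therefore the one to name.

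**2. Illustration: a marker of drug use only.** Pooled AUC = t × A + (1 − t) × 0.5, where A is the AUC in treated cases. Assume A = 0.95.
- t = 25%: 0.25 × 0.95 + 0.75 × 0.5 = 0.61
- t = 50%: 0.50 × 0.95 + 0.50 × 0.5 = 0.73 (rounded from 0.725)
- t = 75%: 0.75 × 0.95 + 0.25 × 0.5 = 0.84
- Untreated PwP alone: 0.50

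**3. Illustration: a marker that works less well without drugs.** Assume sensitivity of 90% in treated and 60% in untreated cases.
- t = 20%: 0.2 × 0.90 + 0.8 × 0.60 = 66%
- t = 50%: 0.5 × 0.90 + 0.5 × 0.60 = 75%
- t = 80%: 0.8 × 0.90 + 0.2 × 0.60 = 84%
- Untreated PwP alone: 60%

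**4. Are there enough untreated PwP?** RQ1 gives populations for Ghana (113,114), Kenya (300,000) and Tanzania (180,000), in total 593,114. Lagos is left out because the size of its subset is not given. Assume 20 to 60 PD cases per 100,000.
- 593,114 × 20/100,000 = 119 cases; 593,114 × 60/100,000 = 356 cases
- With 75% undiagnosed (the bound implied by the Hai statement, applied to all three sites): 119 × 0.75 = 89; 356 × 0.75 = 267

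This is an upper-side count for these sites. It equates undiagnosed with untreated and supposes that everyone consents and gives samples. Against the 1000 PwP samples intended for DNA work (RQ2 a), and only if sebum and stool sampling is of similar size, it is about 9% to 27% of cases.

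**5. Is the timing fixed?** Both outcomes are set at baseline, but baseline is not defined relative to the first PD drug. Study components places biological sampling at a clinic visit, and RQ1 registers people with a diagnosed neurological condition at the local clinic for follow-up care. The order of sampling and treatment is left open.

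**The case against.** The strongest reply is that the planned data already allow the separation. Medication use is asked about, stage is scored, samples are linked to phenotype, survey-diagnosed PwP are invited and multivariable modelling is foreseen. Choosing the subgroup to prespecify is something that a condensed article may leave to a full protocol or SAP not shown here. **This stands in large part.** A reader might infer that a drug signature can never be told from a disease signature in this project. The documents do not support that; only the stated primary contrast, taken alone, fails to separate them.

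Other points with weight:
- The sebum sentence can be read mainly as asking whether a known signature carries over to African populations. It does ask that, but it also asks whether the signature is purely disease-related, and the pooled contrast does not answer that part.
- Late-stage change is not confounding. It is part of the disease and raises a question of case spectrum. Stage is recorded, and PwP too disabled by advanced disease to complete procedures are excluded. So stage calls for reporting by stratum and does not invalidate the contrast.
- The treated share is unknown, and the Background describes medication as hard to obtain or afford. A low treated share would shrink the problem, as steps 2 and 3 show.
- Trial entrants are not all never-treated: the RQ6 inclusion criteria admit up to 6 months of earlier levodopa if stopped at least 3 months before.
- Making untreated PwP the sole primary comparison would set aside many cases and lean on the four survey countries. That trade-off is debatable and is not needed.

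**Conclusion.** The concern holds in limited form. The primary sebum and microbiome outcomes are pooled over treatment status and stage, PD drugs almost certainly occur only in cases, and the pooled result alone can support neither a disease-only signature nor a claim about accuracy in untreated people. The means to answer both questions are already in the project; what the article lacks is a named comparison and a defined sampling order. This is a worthwhile, low-cost improvement rather than a failure of the design.

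The size is not known. The AUCs of 0.61 to 0.84 against 0.50, the sensitivities of 66% to 84% against 60%, and the 89 to 267 undiagnosed cases all rest on assumed inputs and are not forecasts. The structural conclusion needs only two things: some sampled PwP are on PD drugs, and no control is.

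**What to change.** - **Keep** the pooled contrast for both sample types.
- **Add a prespecified key comparison:** PwP not exposed to PD drugs versus their matched controls. As support, compare treated with untreated PwP at similar stage.
- **Define baseline.** For newly diagnosed survey cases and trial entrants, state that stool, buccal and sebum samples are taken at the diagnostic or baseline visit already planned, before any PD drug where this does not alter care. Record the date of first PD drug and of sampling.
- **Record earlier levodopa exposure** in trial entrants. Processes for recruitment calls them treatment naïve while the RQ6 criteria allow limited earlier use; the two passages should be reconciled, and the untreated group defined from the recorded exposure.
- **Report** diagnostic accuracy by treatment status and by stage.
- **Tie the claim to the evidence:** call a signature disease-related only if it holds in the untreated group.

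The cost is analysis wording and sample timing at planned visits, with data already to be collected. The untreated comparison will have fewer cases, come mainly from the four survey countries and be less precise, so its confidence interval should be reported and its reach stated modestly.
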